**Timing of elective caesarean section and neonatal morbidity - a randomised multicentre trial.**

1. **Working Title**

Comparison of neonatal morbidity after elective caesarean section at 38+3 vs. 39+3 weeks: a randomised controlled multicentre study.

1. **Background**

Elective (planned) caesarean section accounted for approx. 10% of all births in Denmark in 2007. The caesarean section rate continues to rise globally (Villar et al.), which in part can be attributed to a rise in the number of caesarean sections performed without medical indications, i.e. upon maternal request.

Elective caesarean section (ECS) is scheduled prior to or at 39+0 gestational weeks at several Danish hospitals (Sandbjerg guidelines, personal communications). This is probably because the number of unscheduled or acute caesarean sections increases with scheduling closer to the due date due to an increase in women with spontaneous onset of labour prior to the scheduled date. It has been suggested that 10-17% of pregnant women will go into labour before 39+0 weeks (NICE, Hansen, Morrison). Previous studies have found an increased risk of maternal perioperative and postoperative complications with acute caesarean sections, but whether an increased risk also exists among women delivered by an acute, originally planned caesarean section is uncertain (van Ham, Allen).

Several observational studies reported an increased risk of neonatal respiratory morbidity with earlier term gestational ages (Hansen, Morrison, Zanardo). The incidence of neonatal admission after ECS without a medical indication may be 13.1% (Yee) or approximately 14% at 38+0-38+6 weeks, decreasing to 8% at 39+0-39+6 weeks (Hansen). Hansen et al. found a decreasing risk of respiratory morbidity in infants born by ECS from 37 to 39 weeks. Compared with neonates of the same gestational age delivered vaginally, the risk of respiratory morbidity was no longer significantly increased in neonates delivered after 39 weeks. No randomised studies have yet evaluated respiratory morbidity or complications requiring hospitalization of the neonate following ECS in the immediate pre-term weeks.

Admission to a neonatal ward is an evident burden, both for the family and from a health economic perspective. So is any complication from caesarean section suffered by the mother. This testifies to the need for a randomised study of the timing of term ECS to ensure optimum timing of caesarean section with minimal risk of complications for mother and child. In addition, such study would shed light on the important organizational aspect of optimizing the gynaecological ward and the maternity ward routines.

**3. Aim of study** 
The aim of this study is to compare ECS scheduled at 38+3 weeks and ECS scheduled at 39+3 weeks with respect to neonatal and maternal adverse events, with respect to organisational aspects of initially planned, unscheduled caesarean sections, and with respect to maternal satisfaction with timing of the procedure.

**3.1 Null hypotheses**

1. That there is no difference in neonatal morbidity measured as the incidence of NICU admission, infection and respiratory morbidity.
2. That there is no difference in infant morbidity (health care utilization) within the first two months and the first two years of life.
3. That there is similar maternal perioperative and postoperative morbidity between the two groups.
4. That women's satisfaction with timing of the ECS do not differ between the two groups.
5. That there is no difference in the incidence of maternal depression between the two groups.

**4. Method and materials** 
Open-label randomised multicentre trial. 
The pregnant women are assigned to one of two treatments: 

1) ECS at 38+3 weeks (range 38+1 to 38+5) 
2) ECS at 39+3 weeks (range 39+1 to 39+5) 

The pregnant woman is included at any stage of her pregnancy when planning ECS in consultation with her obstetrician. The obstetrician assesses her eligibility based on the inclusion and exclusion criteria. At the preliminary examination in the pre-natal clinic, the obstetrician fills in a worksheet to obtain the following information: Name, social security number, indication for caesarean section, date of confinement, age > 18 years, due date according to the nuchal translucency scan, singleton pregnancy, diabetes, if pregnancy may be continued to week 39+5, use of interpreter to communicate in Danish, smoking status, height, weight, and parity. Information on both participants and non-participants are collected.

The obstetrician provides oral and written project information to the woman and obtains written consent. The latter task may be performed by a project staff nurse or midwife.
Between seven and eight weeks after birth, an e-mail with a link to a questionnaire is sent to the participant who will be asked for permission to contact her at a later time in case any new research emanates from the material.

The pregnant woman will be excluded if she submits a request to this effect, and any change in the date of planned caesarean will be at the discretion of the local administrator. However, exclusion of the woman’s data from the study does not take place at any time after consent has been obtained as data are analysed by the intention-to-treat principle.

**4.1 Outcomes**

Primary outcome:

- Neonatal morbidity causing admission to neonatal ward within the first 2 days of life

Secondary outcomes:

1. Admission to neonatal unit within 7 days after birth
2. Neonatal length of stay and ICD-10 diagnoses for hospitalized children
3. Neonatal treatment and duration of treatment: Mechanical ventilation, CPAP, oxygen supplementation, intravenous antibiotics
4. Outpatient treatment or control, or admission to a neonatal unit or paediatric ward within 2 months or 2 years after birth
   1. Department or physician, date of admission and discharge, ICD-10 codes, treatment, type of medical treatment.
5. Maternal morbidity within 30 days
   1. Perioperative complications: Uterine incision lateral tear, blood loss, laceration of bladder or intestine, other intraoperative complications
   2. Postoperative complications: Blood transfusion, need of re-operation, antibiotic treatment, and total hospital stay.
6. Logistics
   1. Acute caesarean section (8 hours from decision to execution)
   2. Reason for acute caesarean section: labour, PROM, foetal indication, pregnancy complications, maternal request
   3. Time of delivery
   4. Education & training of operating physicians
7. Child’s nutritional status after 2 months
8. Mother’s preference for time of caesarean at any subsequent pregnancy.

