**5. Power calculation**
The sample size is calculated on the basis of the primary endpoint of neonatal ward admission within the two days after birth, using data from an existing birth cohort from the same population. Approx. 14% of those delivered by early caesarean section and 8% of those delivered by late caesarean section are hospitalized. With a significance level of 5% and a power of 0.80, the calculated sample size is 459 in each group. With non-compliance of around 9%, the total number of enrolled participants is calculated to approx. 1,270 women.

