**7. Data processing and analyses** 
Data collected from the two groups are used in a comparative analysis to identify any inter-group differences on the specified parameters. 
Statistical variables will be calculated according to the intention-to-treat principle and per-protocol using the analytical software program STATA. The primary endpoint will be analysed with a 5% significance level. The budget foresees the need for a statistician to assist with the data analyses.

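### Length of stay is compared only among hospitalised children, a group formed after randomisation that timing is expected to change, so the result may be null or reversed when early section adds hospital days.

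*Protocol*

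**What the plan says.** Protocol section 4.1 gives the primary outcome as "Neonatal morbidity causing admission to neonatal ward within the first 2 days of life". Secondary outcome 2 is "Neonatal length of stay and ICD-10 diagnoses for hospitalized children". Secondary outcome 3 is "Neonatal treatment and duration of treatment: Mechanical ventilation, CPAP, oxygen supplementation, intravenous antibiotics", with no population stated.

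Section 7 says how the outcomes are used: "Data collected from the two groups are used in a comparative analysis to identify any inter-group differences on the specified parameters". It adds: "Statistical variables will be calculated according to the intention-to-treat principle and per-protocol".

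Section 5 gives the expected admission rates: "Approx. 14% of those delivered by early caesarean section and 8% of those delivered by late caesarean section are hospitalized".

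The protocol does not define length of stay over all randomised infants, does not count infants who are not admitted as zero days, and does not label the figure as descriptive.

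**The concern.** Randomisation makes the two arms comparable as whole arms. It does not make the hospitalised infants of one arm comparable with those of the other when the allocated timing affects who is hospitalised, and the trial is planned on the expectation that it does.

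If early section brings in infants who would not have been admitted after late section, they change the mix of the early subgroup. Suppose these extra infants mostly have short stays. The early average among admitted infants then falls, although the early arm as a whole uses more ward days. A reader could take this as faster recovery after early section. The Background presents neonatal admission as a burden on families and on health-care resources. Mean stay among admitted infants does not measure that burden; days per randomised infant do.

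**Working it through.** **Inputs from the protocol.** Admission 14% early and 8% late, 5% significance, power 0.80, 459 per group, non-compliance about 9%, about 1,270 enrolled (all section 5). That is about 635 per arm. No length-of-stay figure is given.

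**Reproducing the planned sample size.** A two-sided comparison of 14% with 8% at 5% and 80% power gives 426 per group without continuity correction and 459 with it, matching "With a significance level of 5% and a power of 0.80, the calculated sample size is 459 in each group". The enrolment in "With non-compliance of around 9%, the total number of enrolled participants is calculated to approx. 1,270 women" is matched if 9% in each arm are assumed to receive the other timing:
- early: 0.91 × 14% + 0.09 × 8% = 13.46%
- late: 0.91 × 8% + 0.09 × 14% = 8.54%
- required: 634 per arm without continuity correction, 1,268 in total.

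So 14% and 8% are the real planning rates.

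**Size of the selected groups.** With 635 per arm, 0.14 × 635 = 89 early and 0.08 × 635 = 51 late infants enter the restricted comparison. With 459 per arm the numbers are 64 and 37. If every infant admitted after late section would also be admitted after early section, then (14 − 8)/14 = 43% of the early subgroup has no late counterpart. With the diluted rates this is (13.46 − 8.54)/13.46 = 37%.

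**Effect on length of stay (assumed model).** Let 8% be admitted under either timing with mean stay L, the same in both arms. Let a further 6% be admitted only with early section, with mean stay S.
- Among admitted: early (0.08L + 0.06S)/0.14, late L. The difference is 0.06(S − L)/0.14.
- Per randomised infant: early 0.08L + 0.06S, late 0.08L. The difference is 0.06S, positive for every S > 0.

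With L = 5 days (late arm: 5.00 days among admitted, 0.40 per infant, 254 in total):

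| S (days) | Early, among admitted | Early, per infant | Early, total with 635 |
| --- | --- | --- | --- |
| 1 | 3.29 | 0.46 | 292 |
| 2 | 3.71 | 0.52 | 330 |
| 3 | 4.14 | 0.58 | 368 |
| 5 | 5.00 | 0.70 | 444 |
| 7 | 5.86 | 0.82 | 521 |

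For S = 2: (0.08 × 5 + 0.06 × 2)/0.14 = 0.52/0.14 = 3.71. Early looks 26% shorter among admitted infants (3.71/5.00 = 0.74) while using 30% more days per infant (0.52/0.40 = 1.30). At S = 5 the restricted comparison shows nothing, although early section adds 75% (0.70/0.40 = 1.75). At S = 7 its direction is right. With L = 3 or L = 7 the sign again turns at S = L.

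**How often a test would mislead.** A simulation used L = 5, 635 per arm, gamma-distributed stays with shape 1.5 and 2,000 trials per setting. A rank-sum test among admitted infants found a significantly shorter early stay in 93%, 60% and 24% of trials for S = 1, 2 and 3, in 3% for S = 5 and in 0.3% for S = 7. Over all infants with zeros, the rank test found significantly more days in the early arm in 89% to 94% of trials and never the reverse.

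**The case against.** **The entry is an outcome list, not an analysis specification.** A ward stay exists only for an admitted child, so the qualifier may describe what is recorded, or may attach only to the diagnoses. The denominator could be set in a statistical analysis plan, which is not shown. This has some force. But the plain reading covers stay and diagnoses alike, section 7 sends the listed parameters to a between-arm comparison, and a later plan would have to depart from the written population to repair it. That is more than missing detail.

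**The reversal is not established.** This stands. No section says that the extra early admissions would be shorter, and the model assumes that timing leaves the stay of the other 8% unchanged. If early section lengthened their stay by d days, reversal would need 0.08d < 0.06(L − S); with L = 5 and S = 2, d below 2.25 days. A reader might infer that the restricted figure will favour early section. The documents support only that it can.

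**Secondary outcome 3.** A reader might infer that treatment durations are restricted too. The text does not restrict them. The same problem arises only if durations are compared among treated infants.

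**Intention to treat.** A reader might infer a contradiction with the intention-to-treat statements in sections 4 and 7. These concern keeping women's data and analysing by assigned arm, and a subset can be tabulated by assigned arm without breaching their wording. They do not, however, undo selection on an event after randomisation.

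**Admission rates are reported alongside.** Admission within 2 and 7 days are separate outcomes, so a careful reader could see both. That softens the harm but does not make the stay comparison valid.

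**Conclusion.** The point holds for secondary outcome 2. As defined, it compares stay and diagnoses in groups selected by an event that the trial expects to differ by arm, with roughly 37% to 43% of the early subgroup lacking a late counterpart under the protocol's rates. The comparison can give the wrong sign (S < L), no difference (S = L) or the right direction (S > L), while the per-infant difference is 0.06 × S days in each case. The rates come from the protocol. The stays, the unchanged stay of the 8% and the nesting of late admissions within early ones are assumptions.

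Two limits apply. Hospitalised children are not exactly those meeting the primary outcome, since admission after day 2 may also count. And this is a secondary outcome, so the primary analysis is unaffected. The definition should be corrected, but the trial's main conclusion does not depend on it.

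**What to change.** Define secondary outcome 2 as neonatal-ward days per randomised infant, with 0 for infants not admitted. Compare mean days by assigned arm with a bootstrap or permutation interval. Compare each diagnosis as a proportion of all randomised infants. Keep stay among admitted infants as a descriptive figure without a test. For secondary outcome 3, state only that treatments and durations use the same all-randomised denominator, with 0 for untreated infants.

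The cost is wording: the same data are used with zeros filled in. The drawback is that about 86% of early and 92% of late values would be zero, so the per-infant mean partly repeats the admission difference already tested. It should be read as a measure of total burden, not of severity once admitted.

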**4.4 Data collection**
Data are retrieved from the individual patient records and are entered into a study data registration form. 
Data regarding the child's progress within 2 months and 2 years after birth are retrieved either from medical records on the data registration form or are extracted from the Danish National Board of Health's national patient Register using the relevant personal security numbers (CPR). 
Data from the registration form are entered into EpiData by a secretary at the Perinatal Research Unit. Data from the questionnaire are downloaded from the server (Ramboll, SurveyXact). 
Data are kept confidential and in accordance with Danish Law. Obstetricians in charge of the study at each facility and project staff are responsible for correct data handling and storage. The project has been approved by the Danish Data Protection Agency.

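### Secondary outcome 4 contains the primary event, so a difference at 2 months or 2 years cannot by itself be attributed to anything after the first week; a comparison of contacts starting after day 7 should be added.

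*Protocol*

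**What the plan says.** Section 3.1 separates two questions about the child. Null hypothesis 1 is "That there is no difference in neonatal morbidity measured as the incidence of NICU admission, infection and respiratory morbidity". Null hypothesis 2 is "That there is no difference in infant morbidity (health care utilization) within the first two months and the first two years of life".

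Section 4.1 gives three outcomes with nested time windows, all starting at birth:

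- Primary: "Neonatal morbidity causing admission to neonatal ward within the first 2 days of life".
- Secondary outcome 1: "Admission to neonatal unit within 7 days after birth".
- Secondary outcome 4: "Outpatient treatment or control, or admission to a neonatal unit or paediatric ward within 2 months or 2 years after birth".

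Outcome 4 has no later start and does not exclude the birth stay. The items recorded under it are "Department or physician, date of admission and discharge, ICD-10 codes, treatment, type of medical treatment". Section 4.4 names medical records or the national patient register as the source of these data.

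Section 5 sizes the trial on the primary endpoint: "Approx. 14% of those delivered by early caesarean section and 8% of those delivered by late caesarean section are hospitalized".

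**The concern.** A hypothesis listed separately from neonatal morbidity would be expected to add something to it. As outcome 4 is defined, an admission in the first 2 days meets the primary outcome, secondary outcome 1, and outcome 4 at both 2 months and 2 years. (This takes the neonatal ward of the primary outcome and the neonatal unit of outcomes 1 and 4 to be the same place.) The trial expects more such admissions after early section, so a difference on outcome 4 is what its own planning assumptions predict, even if the two groups are identical from the second week on.

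At stake is interpretation. One short-lived event could be reported as a difference at 2 days, 7 days, 2 months and 2 years, and the last two could be taken for lasting effects on infant health.

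**Working it through.** **Inputs from the protocol.** Primary event 14% (early) v 8% (late), 5% significance level, power 0.80, 459 per group, about 1,270 enrolled (all section 5).

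**Assumptions.** The test is two-sided. Allocation is 1:1, so 1,270 / 2 = 635 per arm. Outcome 4 is analysed as the proportion of infants with any qualifying contact. The rate q of contact after the newborn period is the same in both arms and independent of early admission. The protocol gives no value for q, so a range is shown.

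**Reproducing the plan's figure.** A two-sided 5% comparison of 14% v 8% with 80% power and continuity correction needs 459 per group, as stated (426 without the correction).

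**Carry-over.** With early-admission risk p, the risk of any contact is

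P = 1 − (1 − p)(1 − q).

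At q = 10%: early 1 − 0.86 × 0.90 = 22.6%; late 1 − 0.92 × 0.90 = 17.2%. In general the difference is (0.14 − 0.08)(1 − q) = 0.06(1 − q), here 5.4 points. All of it comes from the primary event.

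**Chance of a significant result.** Without continuity correction this is Φ((d − 1.96·SE0)/SE1), where d is the difference, SE0 the pooled and SE1 the unpooled standard error. At q = 10% and n = 635: SE0 = √(2 × 0.199 × 0.801 / 635) = 0.0224; SE1 = √((0.226 × 0.774 + 0.172 × 0.828) / 635) = 0.0224; (0.054 − 1.96 × 0.02241) / 0.02236 = 0.45; Φ(0.45) = 0.67.

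| Assumed q | Early v late | Difference (points) | Chance at 459 per arm | Chance at 635 per arm |
|---|---|---|---|---|
| 5% | 18.3% v 12.6% | 5.7 | 67% | 80% |
| 10% | 22.6% v 17.2% | 5.4 | 54% | 67% |
| 20% | 31.2% v 26.4% | 4.8 | 36% | 47% |
| 40% | 48.4% v 44.8% | 3.6 | 19% | 25% |
| 70% | 74.2% v 72.4% | 1.8 | 9% | 11% |

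**Sensitivity to crossover.** If 9% in each arm have the other arm's timing, the primary rates become 0.91 × 14% + 0.09 × 8% = 13.46% and 0.91 × 8% + 0.09 × 14% = 8.54%. At 635 per arm and q of 5%, 10%, 20% and 40%, the chances fall to 63%, 51%, 34% and 18%.

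**After the change.** If only contacts beginning after day 7 count, the true difference in this scenario is zero and the chance of significance is the nominal 5%.

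**The case against.** The strongest reply is that outcome and hypothesis agree. Null hypothesis 2 concerns health-care use within the first two months and two years of life, which is cumulative from birth. If early admission is 14% v 8%, cumulative use does differ, and rejecting the hypothesis is correct. This stands. A reader might infer that the chances above are false-positive rates that ought to be 5%. The protocol does not support that reading: 5% would apply to a null about contacts after the newborn period, which the protocol does not state.

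A reader might also infer that the trial cannot show whether timing affects later infant health. That goes too far. Departments, admission and discharge dates and ICD-10 codes are recorded under outcome 4, so early and later admissions can be separated. The limitation lies in the outcome as defined, not in the data.

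It is also tempting to say that check-ups after neonatal discharge make the carry-over worse. In an any-contact analysis they add nothing, because those infants are already counted. They could matter for a count of contacts, which was not modelled. They are also real health-care use, which is what hypothesis 2 names.

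The size at 2 years is uncertain. The carry-over shrinks as later contact becomes common, to about 11% at q = 70%, and no document gives the 2-year rate.

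Finally, the protocol does not fix the statistic for outcome 4, and an analysis plan that is not shown could add a split by date. That limits the point to an improvement. It does not remove it, because the window from birth is stated in the protocol itself, and section 4.3 says data analyses are open, so a start date chosen late would be open to question.

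**Conclusion.** The point holds as a limit on interpretation, not as an error in the stated test. Outcome 4 contains every primary event by definition. It answers hypothesis 2 as worded, but a difference on it at 2 months or 2 years cannot by itself be attributed to anything after the first week.

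The primary event alone would put between 5.7 points (q = 5%) and 1.8 points (q = 70%) into the comparison, with a chance of significance from about 80% down to 11% at 635 per arm. This rests on an any-contact analysis, 1:1 allocation, the protocol's 14% v 8%, and a later-contact rate that is assumed, equal between arms and independent of early admission. The concern is greatest where later contact is uncommon. That is more likely at 2 months than at 2 years, because contacts have had less time to accrue. The outcome is secondary, and the remedy is inexpensive.

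**What to change.** Keep the cumulative count from birth as the answer to null hypothesis 2 as worded. Add a prespecified comparison, in all randomised infants, of admissions and outpatient contacts that begin after day 7, where secondary outcome 1 ends, up to 2 months and up to 2 years. Base any statement about infant health after the newborn period on this added comparison.

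Do not require each check-up to be attributed to the birth admission. That would need a judgement on every contact in an open-label trial, and the start date alone is enough. Paediatric-ward or outpatient contacts in days 0–7 remain in the cumulative count, so nothing is lost.

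The cost is a sentence in section 4.1 and one further analysis. Admission dates are already recorded under outcome 4; the wording should make clear that the date of each outpatient contact is taken as well. The downside is that fewer events count, so the added comparison is less precise.
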